#### The effectiveness of NSEIT/NSE

Background data will be collected, including age, sex, symptom duration, and whiplash injury or other reason for neck pain.

The primary outcome measure that will be collected is neck-specific function as measured by the Neck Disability Index (NDI) [42].

The secondary outcome measurements will be pain intensity (current, average last week, worst pain last week) in the neck, head, and arm, and dizziness (current, average last week, worst dizziness last week) in the past week, using a numeric rating scale (NRS, score 0 to 10: 0 = no pain or dizziness, 10 = worst imaginable pain or dizziness) [43]; answers to questions about health-related quality of life; work ability measured with the Work Ability Score (WAS) reporting “current work ability compared to highest work ability ever” (score 0 to 10; 0 = cannot work at all, 10 = best work ability [44]; and patient’s improvement or deterioration over time, measured with an 11-point global rating scale (GRS: − 5 = vastly worse, 0 = unchanged, 5 = completely recovered) [45]. Any adverse events or negative effects will be registered at the 3-month follow-up.

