### NSE and NSEIT - the implementation object

#### Neck-specific exercise with internet support

The internet-based exercise program, NSEIT, is available on-line by phone, tablet, or computer via the Swedish National Support and Treatment Services, INERA. Since 2016, all regions in Sweden have been connected to the Support and Treatment services, a web-based e-health solution to enhance digitalization in health care. The platform is accessed through Health Care Guide 1177 and patients logging in using BankID. The physiotherapists logging in to the Support and Treatment services will choose exercises and information from two different programs, WAD ExerciseIT (for patients with whiplash-associated disorders) and Neck ExerciseIT (for patients with non-specific neck pain). The two programs contain the same neck-specific exercises and the same information about persistent pain, the benefits of exercise directed to the deep neck muscles, strategies for dealing with neck pain relapse, ergonomic advice related to the neck, complementary exercises for shoulder muscles and the low back, and strategies for continuing exercise after the treatment period. WAD ExerciseIT contains information about whiplash injury and Neck ExerciseIT has information about non-specific neck pain and stretching exercises. The physiotherapists will choose and individually progressively assign the neck-specific exercises during the treatment period. In the RCT study, each patient had 4 meetings with the physiotherapist, at weeks 1, 2, 3, and 7, to ensure that the patient performed the exercises as intended [12]. At week 1, the first visit to the physiotherapist included an introduction to the exercise intervention chosen from a clear and written framework of exercises. The physiotherapist introduced exercises aimed to facilitate activation of the deep neck muscles and information about the importance of good body and neck posture to minimize postural strain. At week 2, they introduced isometric neck-specific exercises in supine position and continued them in sitting position. Weeks 3 to 12 involved continued training with gradual progression, using a rubber band in sitting position. The patient could also exercise at a gym, using a weighted pulley or guild board. The physiotherapists will be informed about the four meetings in the RCT study, but in this implementation study the physiotherapists will be free to book appointments with the patients.

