### Measurements

Outcome measurements will be recorded at baseline and after 3 and 12 months. See Fig. 2 for the planned schedule of enrollment, interventions, and assessments, and Table 3 for the relationship between the RE-AIM framework and data collection. All questionnaires will be answered electronically through a website. Physiotherapists and patients will receive a disposable code e-mailed by a project team member to log in to the System Artrologik (Survey&Reports). Patients will answer the baseline and 3-month questionnaires through the Support and Treatment services and the 12-month questionnaire through the System Artrologik. The electronic questionnaire cannot be submitted if the core outcomes are not answered. If a participant does not answer the questionnaire after two reminders (1.5 weeks after it is due and after another 1.5 weeks), a project team member not involved in the randomization will contact the participants and remind them.

**Table 3 Tab3:** RE-AIM framework and data collection

Dimension	Research question	Data Collection
Reach	To what extent do patients with WAD receive NSEIT/NSE in primary care?	Primary outcome Data from the medical record from each included physiotherapy clinic and/or the web-based platform INERA
Effectiveness	Is the NSEIT/NSE program effective at decreasing disability and pain in patients with WAD or non-specific neck pain in primary care? Will the results be the same as in the RCTs at 3 and 12 months of follow-up?	Primary and secondary outcomes. Patient self-reported outcomes. The results will be compared with those of previous studies.
Adoption	To what extent do the physiotherapists apply the NSEIT/NSE to patients with WAD or non-specific neck pain?	Secondary outcomes Physiotherapist-reported outcomes. Qualitative methods
Implementation	To what extent is the intervention delivered according to the NSE protocol (fidelity)?	Qualitative methods
Maintenance	To what extent will physiotherapists be continuing to use NSEIT/NSE at the 12-month follow-up?	Secondary outcomes Physiotherapists reported outcomes Qualitative Methods

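### Adverse events are registered at 3 months only, while effectiveness is followed to 12 months; after month 3, harm shows only indirectly through the outcome scales

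*Protocol article*

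**What the plan says.** The section The effectiveness of NSEIT/NSE gives one sentence to harms: "Any adverse events or negative effects will be registered at the 3-month follow-up".

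The general schedule under Measurements is wider: "Outcome measurements will be recorded at baseline and after 3 and 12 months". The route for patients is also set there: "Patients will answer the baseline and 3-month questionnaires through the Support and Treatment services and the 12-month questionnaire through the System Artrologik". A 12-month patient form therefore already exists.

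The description of the internet-supported program lists, as content of both versions, "strategies for continuing exercise after the treatment period". It describes the earlier randomised trial as a 12-week course ("Weeks 3 to 12 involved continued training with gradual progression, using a rubber band in sitting position") and adds that "in this implementation study the physiotherapists will be free to book appointments with the patients".

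The aims ask about effectiveness at both 3 and 12 months. The statistical analysis section models NDI, pain intensity, headache and dizziness at baseline, 3 and 12 months. The secondary outcomes include "patient’s improvement or deterioration over time, measured with an 11-point global rating scale", whose lowest score means vastly worse.

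**The concern.** Harms have been given a narrower window than benefit. This is a stated choice of time point, not a detail left to a fuller document: the general schedule has two follow-up occasions, and the sentence on adverse events picks one of them.

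What is at stake is the balance of the final report. If the program looks effective at 12 months, readers will want to know what it cost patients over the same 12 months, and the registered record would answer only for the first 3. The programs encourage patients to go on exercising by themselves, so later events related to the exercises are possible. The study also admits adults with neck pain in general, whereas the Research needs section says the earlier evaluations were in chronic whiplash-associated disorders. Experience from those trials does not fully cover the patients added here.

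**Working it through.** The protocol gives no figure on this point to reproduce. The check is the length of the gap and what the other measures can see within it.

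**Inputs**
- Adverse-event registration: month 3 (The effectiveness of NSEIT/NSE).
- Last patient follow-up: month 12 (Measurements).
- Patients to be included: 500 (Sample size), used for illustration only.

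**Length of the gap**
- Months after the registration point: 12 − 3 = 9.
- Share of follow-up: 9 / 12 = 75%.
- If all 500 were followed for the full year (an assumption that ignores dropout): 500 × 9 = 4,500 of 500 × 12 = 6,000 patient-months. Uniform dropout before month 3 would lower both numbers but leave the share at 75%.

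This is a share of calendar time, not of exposure or risk.

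**What the 12-month data would show for an event arising after month 3**

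| Kind of harm | Visible at month 12? | Through what |
|---|---|---|
| Neck disability, pain, headache or dizziness that worsens and stays worse | Yes, as a score | NDI, NRS |
| The patient feels worse overall | Yes, as a score | Global rating, which runs to −5 |
| A flare that resolved before the final week | Not on the NRS | The NRS covers only the present and the past week |
| An event outside neck, head or arm pain and dizziness | Not as an event | No dedicated item; at most a lower quality-of-life, work-ability or global score |
| The patient's view that the exercises caused it | No | None of these scales asks for a cause |

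The first two rows are covered and the last three are not. Worsening in the first two rows also appears as a score that enters a group analysis. The Sample size section pools treated patients from both arms into one group, so an average improvement can coexist with harm to individuals.

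**Effect of the change**

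Repeating the item at month 12 extends the registered window from 3 of 12 months (25%) to 12 of 12. No sample size, power or significance level changes.

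**The case against.** The strongest reply is that month 3 is a sensible time to ask. The course in the earlier trial ran to week 12, and the abbreviation list defines NSE as a 12-week program, so the 3-month follow-up covers the main treatment period. Later exercise is self-management with no stated amount or duration. With no untreated comparator, linking a late event to the exercises would be weak even if it were recorded. All of this stands, and it is why the point is minor. It does not remove the mismatch between a 12-month claim of benefit and a 3-month record of harms.

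A second reply is that the sentence does not say only. The schedule figure is not shown, and the article condenses a fuller protocol, so another time point may exist. That is possible, but the article's text gives one time point and nothing in it suggests another.

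Some stronger readings are tempting and are not supported:
- **Harms after month 3 go wholly unseen.** They do not. Sustained worsening would appear at 12 months in the NDI, the NRS and the global rating.
- **Treatment has no fixed end because booking is free.** That sentence contrasts free booking of visits with the four set meetings in the earlier trial. It concerns visits, not the length of the program.
- **Patients who stop because of a negative effect will not answer.** Nothing in the protocol says so, and Measurements provides two reminders followed by contact from the project team.
- **A given number of patients with harm would be missed.** The protocol gives no event rate, so any such count would rest on an invented one.

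**Conclusion.** The point holds as a limited gap in harms reporting. Registration of adverse events is stated for month 3 alone, leaving 9 of 12 months (75% of follow-up time) in which harm is visible only indirectly. What goes unrecorded is transient or resolved events, events outside the scales, and patient attribution. How many patients this concerns cannot be estimated from the document.

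The conclusion rests on two assumptions: that the single named time point is the complete schedule for adverse events, and that the global rating follows the general schedule and so is collected at 12 months. If the unshown figure lists adverse events at 12 months too, the point falls away and the text merely needs to say so. The implementation outcome, the NDI analysis and both sample size calculations are untouched. It is a worthwhile improvement, not a flaw that threatens the trial.

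**What to change.** Repeat the 3-month adverse-event item, in the same wording, in the form the protocol already sends ("the 12-month questionnaire through the System Artrologik"), asking about the time since the 3-month follow-up, and amend the sentence on adverse events to name both time points. Report the two periods separately, because the later answer rests on a 9-month recall and will pick up brief or mild events less reliably than the first.

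The cost is one more question in an electronic questionnaire, a small amendment, and the weaker recall just described.

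If the item cannot be added, state in the protocol and in the report that the harms conclusions apply to the first 3 months only, and that later worsening was assessed only through the NDI, the NRS and the global rating. That costs one sentence.

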#### Qualitative study

To further evaluate the implementation strategy, two qualitative studies will be conducted. Data will be collected from semi-structured focus group discussions with a purposeful sample of physiotherapists who have participated in the study. Physiotherapists from both groups—group A with increased implementation support, and group B with no further support after the first three on-line instructional sessions and one practical instructional session—will be included. Physiotherapists of both sexes and varied ages and professional experiences will be sought. Six focus group discussions with 3–5 physiotherapists in each group will be held 1–2 months after the implementation activity and approximately 1 year after. The focus group discussions will be conducted digitally as a video conference meeting with a secure digital system (Visiba care). Data will be analyzed with qualitative content analysis and an inductive approach for category development, and alternatively with a deductive-inductive approach [46].

The interview guides will include questions about, for example, the physiotherapist’s experiences instructing patients in neck-specific training, which patients they have treated using the neck-specific exercises programs, experiences dealing with patients with neck pain after the implementation of neck-specific exercises, and experiences with implementation support.

### Statistical analyses

All analyses will be conducted in collaboration with a statistician. Data will be analyzed according to intention to treat and supplemented with per protocol analysis. An analysis will be done of the missing data. Imputation methods may be used when deemed to have additional value. Subgroup analyses of age, gender, neck pain intensity, headache, and dizziness may possibly be performed.*Data regarding the implementation strategy* will be analyzed using a parametric t-test and a linear mixed model or repeated-measures ANOVA or the non-parametric Mann-Whitney U test and Kruskal-Wallis test, depending on the data. Analyses will evaluate differences between groups A and B and changes in variables over time.*Data regarding the effectiveness of NSEIT and NSE* will be analyzed with a linear mixed model or repeated-measures ANOVA or Kruskal-Wallis, depending on the data. NDI, pain intensity, headache, and dizziness will be evaluated as dependent variables with time as an independent fixed factor (baseline, 3 months, and 12 months after start of intervention). The results will be compared with the results from the RCT studies [8, 12].

The effect of neck-specific exercises in the present study for WAD grades II and III and for patients with other neck-pain disorders will also be evaluated and compared with the results in the RCT studies [8, 12].

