### Procedure

The 20 physiotherapy clinics will be randomized to 2 groups, stratified for the number of physiotherapists working at the clinic (≥4 physiotherapists or 3 physiotherapist). A computerized block randomization list, conducted by a statistician and allocated by a project team member, will be used. The randomization will be performed by an independent researcher. The researcher sends an e-mail to all physiotherapists at the clinic, containing information about the randomization group. Due to the nature of the study can the physiotherapist not be blinded. Any change in the protocol will be communicated with the ethics committee and if approved appropriate changes will be made in the ClinicalTrial.gov Registry.

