#### Primary outcome

The primary outcome will be the proportion of patients with neck pain receiving neck-specific exercise during the intervention period. Data will be collected from each included physiotherapy clinic, based on each physiotherapist’s registered ICD-10 code (S134, S134A, S134B, S134C, T918, M501, M502, M503, M530, M531, M542) in the medical record.

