### Sample size

Sample size and power regarding group differences were calculated by a statistician. The aim of the study is to evaluate both implementation and effectiveness. The sample size calculation to evaluate implementation was based on the assumption that 15% more patients will receive neck-specific exercises in the intervention group (40% in the intervention group and 25% in the control group). The required sample size under individual randomization will be 150 patients in each arm. With 10 physiotherapy clinics (clusters) in each arm (a total of 20 clusters), intra-cluster correlation of 0.02 and a cluster size of 21 patients, a total of 420 patients will be recruited for 80% power and a significance level of 0.05. To ensure that enough people are in each group after dropouts, a total of 500 patients will be included, 25 patients from each cluster.

Sample size calculation to evaluate effectiveness was based on a clinically relevant improvement of 7% in the NDI, an effect size of 0.2 (Cohen’s f) or 0.4 (Cohen’s d), a correlation among repeated measures of 0.3, and the need for a total of 56 participants for 80% power and a significance level of 0.05. With an expected dropout rate of 20%, a total of 70 participating patients will be needed. The total number of patients may be more than 70 because patients will be recruited at each clinic.

Repeated-measure ANOVA or a linear mixed model will be used to examine changes in the patient-reported outcomes over time (i.e., at baseline and 3 and 12 months). The results will be compared with the results from the RCT studies [8, 12]. Patients who are included in both the intervention and control implementation groups and receive neck-specific exercises will be treated as one group in terms of the effect of the intervention. Analyses will be performed with parametric statistics if assumptions of normality are met, and otherwise with non-parametric statistics.

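### Clinics are randomised within size strata, but the t-test and Mann-Whitney test listed for comparing A with B cannot carry the stratum, which could cost some power if the comparison is made at clinic level

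*Protocol article*

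**What the plan says.** **Design.** Under Procedure, clinics are the unit of randomisation, and allocation is "stratified for the number of physiotherapists working at the clinic (≥4 physiotherapists or 3 physiotherapist").

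**Outcome.** Under Primary outcome (Implementation): "The primary outcome will be the proportion of patients with neck pain receiving neck-specific exercise during the intervention period". It is taken from clinic medical records through diagnosis codes.

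**Analysis.** Under Statistical analyses, the implementation data "will be analyzed using a parametric t-test and a linear mixed model or repeated-measures ANOVA or the non-parametric Mann-Whitney U test and Kruskal-Wallis test", the choice depending on the data. The purpose is given as: "Analyses will evaluate differences between groups A and B and changes in variables over time". The section does not say which listed method serves the primary proportion, or whether its unit is the clinic or the patient. The size stratum appears in no analysis.

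**Sample size.** The assumed rates are "40% in the intervention group and 25% in the control group". The calculation continues: "With 10 physiotherapy clinics (clusters) in each arm (a total of 20 clusters), intra-cluster correlation of 0.02 and a cluster size of 21 patients". It allows for clustering but makes no use of the strata.

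**The concern.** Stratified allocation balances clinic size across the arms, so differences between small and larger clinics drop out of the true sampling variance of the A-minus-B difference. A two-sample test on clinic proportions does not know this: it leaves the between-stratum spread in its error term. If clinic size predicts how many patients receive the exercises, the estimated standard error is then too large, the confidence interval too wide, and the actual type I error below 5%. The design has paid for stratification and the analysis does not collect the benefit. With 20 clinics there is little power to give away.

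This is separate from the handling of clustering: it remains even when the test is correctly done on 20 clinic proportions.

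**Working it through.** **1. The plan's own figure.** For 40% versus 25%, two-sided 5%, 80% power, the unpooled formula gives (1.960 + 0.842)² × (0.24 + 0.1875) / 0.15² = 149.1 per arm, and the pooled formula gives 152. The plan has 150. Design effect: 1 + (21 − 1) × 0.02 = 1.4. Then 150 × 1.4 × 2 = 420, as stated. The figure reproduces (the plan does not state sidedness; two-sided fits).

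**2. What the stratum could remove.** The mean of p(1 − p) over the arms is (0.24 + 0.1875)/2 = 0.21375.
- Variance of a clinic proportion: 0.21375 × 1.4 / 21 = 0.01425.
- Between-clinic part: 0.02 × 0.21375 = 0.004275.
- Ratio: 0.004275 / 0.01425 = 0.30.

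Clinic size can therefore remove at most 30% of the variance of a clinic proportion. How much of that 30% it does remove is not in the article and is varied below as an assumption (the share).

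**3. Power by noncentral t, 21 per clinic, 10 clinics per arm.** The standard error is the square root of the sum over arms of p(1 − p)[0.02(1 − share) + 0.98/21]/10.
- No stratum, 18 df: standard error 0.0534, noncentrality 0.15/0.0534 = 2.81, power 75.7%.
- Stratum in the model, 17 df: 75.4% at share 0, 76.7% at 10%, 78.6% at 25%, 81.9% at 50%, 85.2% at 75%.

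This slightly overstates the gain, because it holds the unadjusted power at 75.7% for every share. Simulation does not.

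**4. Simulation of clinic proportions.** Beta-binomial, 40,000 runs (8,000 for Mann-Whitney), 21 per clinic, an assumed 10/10 split of clinics between strata, balanced by arm. Type I error / power, in %:

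| Share | t-test, no stratum | Regression on group + stratum | Mann-Whitney |
|---|---|---|---|
| 0 | 4.9 / 74.7 | 4.9 / 74.4 | 4.2 / 70.4 |
| 25% | 4.1 / 75.7 | 4.9 / 78.3 | 3.7 / 72.2 |
| 50% | 3.4 / 76.4 | 4.9 / 81.6 | 3.0 / 72.3 |
| 75% | 2.7 / 77.0 | 5.0 / 84.9 | 2.2 / 71.6 |

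For the t-test, adjusting changes power by −0.3, +2.6, +5.2 and +7.9 points. A 14/6 split at a 50% share gives much the same: 75.7% unadjusted, 80.8% adjusted.

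**5. What these shares mean.** With an even split, the gap between strata is 2 × √(share × 0.004275): about 4, 6.5, 9 and 11 percentage points at shares of 10, 25, 50 and 75%. The planned treatment effect is 15 points.

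**6. The same comparison on patients.** If clustering is ignored and size has no effect, the test statistic is inflated by √1.4, so the type I error is 2 × [1 − Φ(1.96/√1.4)] = 9.8%. In the simulation it is 9.8, 8.5, 7.3 and 6.0% at shares of 0, 25, 50 and 75%. That is anti-conservative, the opposite direction.

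**The case against.** The strongest reply is that the article does not exclude the stratum. It condenses a fuller plan, and model covariates are commonly settled in a statistical analysis plan. The same sentence names a linear mixed model, which could carry clinic size as a fixed effect, and the remark about group differences and change over time describes questions, not a closed list of model terms. Nothing ties the primary proportion to the t-test or Mann-Whitney; the sentence also covers scales such as practitioner confidence. All of this stands. A reader might infer that the plan has decided to ignore the stratum, or that its primary test is conservative. The text supports neither: no test is fixed for the primary outcome, nor is the unit of analysis.

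The size of the loss also rests on a share the article does not give, and nothing in it shows that clinics with 3 physiotherapists differ from larger ones. That stands too, which is why only a range is offered.

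Finally, 21 per clinic is the plan's figure after dropout. At the 25 per clinic to be recruited, the unadjusted clinic-level calculation gives 80.5% power, and an outcome taken from medical records need not suffer questionnaire dropout. So a reader should not infer from the 75.7% that the trial is underpowered for want of the stratum. That figure reflects 21 per clinic and a t reference distribution on 18 df.

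What survives is narrower. The section is not silent on method: it lists tests that cannot reflect the stratified design, and for a single proportion over one period these are natural candidates.

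**Conclusion.** The point holds conditionally. Some methods listed for the A-B comparison cannot carry the randomisation stratum, and the one that most readily can is not said to. If the primary proportion is compared at clinic level by an unadjusted test, and clinic size is prognostic, the test is conservative. The power loss is then about nil at a share of 0, 1 point at 10%, 2.5 points at 25%, 5 points at 50% and 8 points at 75%. This assumes the plan's rates, an intra-cluster correlation of 0.02, 21 per clinic and an even stratum split. The loss reaches 5 points only if size explains about half or more of the between-clinic variance.

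It would go too far to say that the interval is too wide or the type I error below 5% as the plan stands. Both need a clinic-level test and a prognostic stratum, and the article establishes neither. Run on patients, the same tests would usually be anti-conservative, and that would be the more serious fault. In the clinic-level case the omission causes no bias and no excess of false positives. Low severity; a cheap improvement.

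**What to change.** In Statistical analyses, name one primary analysis for the proportion receiving neck-specific exercise that accounts for clinic and includes the size stratum. Either of these will do:
- a linear regression of the 20 clinic proportions on group and stratum (3, or 4 or more, physiotherapists), with 17 df; or
- a patient-level mixed model with a random clinic effect, group and stratum as fixed effects, and small-sample degrees of freedom.

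If a rank test is wanted, use the stratified (van Elteren) version on clinic proportions in place of Mann-Whitney.

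The change is a sentence of wording, and the stratum is already known for every clinic. The price is one degree of freedom, about 0.3 points of power if clinic size turns out to be unrelated to the outcome.

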## Method

### Design

We propose a prospective cluster-randomized mixed-design study evaluating the implementation strategy and effectiveness of the NSEIT/NSE. The study is based on hybrid 2 trial design, as described by Curran et al. [33], where both implementation and clinical effectiveness are tested simultaneously. This study has been approved by the Swedish Ethical Review Authority (Dnr: 2021-03383, 2021-06016-02, 2022-00479-02) and will be conducted in accordance with the Declaration of Helsinki.

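### The plan randomises and powers by clinic, but its analysis of group A versus group B names neither a clinic effect nor a unit of analysis; run on patients, the t-test or rank tests have a true error rate of about 10–11%

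*Protocol article*

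**What the plan says.** The Design section states: "We propose a prospective cluster-randomized mixed-design study". Under Procedure, "The 20 physiotherapy clinics will be randomized to 2 groups", and the allocation is "stratified for the number of physiotherapists working at the clinic" (three, or four and more).

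For implementation, "The primary outcome will be the proportion of patients with neck pain receiving neck-specific exercise during the intervention period". The same section adds that "Data will be collected from each included physiotherapy clinic", using the diagnosis codes in the medical record.

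The Sample size section allows for the clustering: "With 10 physiotherapy clinics (clusters) in each arm (a total of 20 clusters), intra-cluster correlation of 0.02", 21 patients per clinic and 420 in total, raised to 500 (25 per clinic) to cover dropout.

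In the Statistical analyses section, the implementation data "will be analyzed using a parametric t-test and a linear mixed model or repeated-measures ANOVA or the non-parametric Mann-Whitney U test and Kruskal-Wallis test", the choice depending on the data. These analyses are to cover both differences between groups A and B and changes over time. The only model term given anywhere is time as a fixed factor, and that belongs to the effectiveness data. Clinic and the clinic-size stratum do not appear in any analysis.

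**The concern.** The sample size treats patients of one clinic as correlated. The analysis section lists tests that, in their usual patient-level form, treat all observations as independent. The t-test, the Mann-Whitney test and the Kruskal-Wallis test have no place for a clinic effect. Repeated-measures ANOVA as described has none either. The linear mixed model could carry one, but its random effects are not stated, and it is one option among several.

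The comparison of A with B on the proportion receiving neck-specific exercise is the primary implementation test. It is also the trial's main randomised comparison, because the effectiveness data of both groups are pooled and analysed as one group. If patients are the unit, the standard error is too small, and a false claim that extra implementation support works becomes about twice as likely as the stated 5%. If clinics are the unit, the problem disappears. The text does not say which applies.

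**Working it through.** **Inputs, all from the Sample size section:** 40% versus 25%; 150 per arm under individual randomisation; ICC 0.02; 10 clinics per arm; 21 patients per clinic (25 enrolled); 80% power; significance level 0.05. Sidedness is not stated; two-sided reproduces the plan's figures.

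**1. The plan's own figure.** With unpooled variance, n per arm = (1.960 + 0.842)² × (0.40×0.60 + 0.25×0.75) / 0.15² = 7.849 × 0.4275 / 0.0225 = 149.1, in line with the stated 150. The design effect (DE) is 1 + (21 − 1) × 0.02 = 1.40. Then 150 × 1.40 = 210 per arm, or 420 in total. The sample size reproduces, and it rests on the clustering.

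**2. Error rate if clinic is ignored.** A patient-level test understates the standard error by a factor √DE, so its true two-sided error rate is 2 × [1 − Φ(1.96/√DE)].

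| Patients per clinic | DE | 1.96/√DE | True error rate | Coverage of a nominal 95% interval |
|---|---|---|---|---|
| 21 | 1.40 | 1.656 | 9.8% | 90.2% |
| 25 | 1 + 24×0.02 = 1.48 | 1.611 | 10.7% | 89.3% |

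**3. Check by simulation.** Beta-binomial data were generated with 10 clinics per arm, ICC 0.02, no true difference, common proportions of 25%, 32.5% and 40%, and 20,000 trials per scenario.

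| Test | Unit | Rejection rate at nominal 5% |
|---|---|---|
| t-test or Mann-Whitney/Kruskal-Wallis, 21 per clinic | patient | 9.6–10.1% |
| t-test or Mann-Whitney/Kruskal-Wallis, 25 per clinic | patient | 10.5–11.0% |
| t-test, 21 or 25 per clinic | 20 clinic proportions | 4.8–5.3% |
| Mann-Whitney, 21 or 25 per clinic | 20 clinic proportions | 4.0–4.5% |

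The unit of analysis, not the name of the test, decides the result.

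**4. Sensitivity to the ICC (assumed values, not in the article).** At ICC 0.01 the patient-level error rate is 7.4–7.8% for 21–25 per clinic; at 0.03 it is 12.1–13.5%.

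**5. Power of a valid clinic-level test.** With 20 clinics the t-test has 18 df. The standard error is √(0.4275 × DE / (10m)), where m is the number of patients per clinic.
- m = 21: √(0.4275 × 1.40 / 210) = 0.0534; 0.15 / 0.0534 = 2.81; power from the noncentral t is 75.7%.
- m = 25: √(0.4275 × 1.48 / 250) = 0.0503; 0.15 / 0.0503 = 2.98; power is 80.5%.

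Simulation gave 75.8% and 80.5%.

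**The case against.** The strongest reply is that the article never says the tests will be run on patients. The primary outcome is a proportion, the data are gathered clinic by clinic, and a t-test or Mann-Whitney test suits 20 clinic proportions better than yes/no data. On that reading the named tests are valid. The linear mixed model is also listed and could hold a clinic effect. Random effects and degrees of freedom are commonly left to the full protocol or the analysis plan, and the sample size shows that clustering was recognised.

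Much of this stands. A reader might infer that the plan's error rate simply is 10%. The document does not support that, because the inflation depends on a patient-level analysis that it neither states nor excludes. What does not stand is that this is only missing detail. The article commits to a list of tests, leaves the choice to the data, and by doing so admits both a 5% and a 10% test of its primary implementation outcome.

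Other stronger readings also fail:

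- **That the normality rule forces a patient-level rank test.** The sentence "Analyses will be performed with parametric statistics if assumptions of normality are met, and otherwise with non-parametric statistics" closes a paragraph on patient-reported outcomes over time, so it does not clearly govern the primary implementation outcome.
- **That intervals for the Neck Disability Index are too narrow.** This is a within-patient change over time in one pooled group, from which a shared clinic level largely cancels. Nothing in the article allows the remainder to be sized.
- **That physiotherapist scores are badly affected.** If the ICC is also 0.02 and there are 3–5 physiotherapists per clinic (assumptions; the article gives only a minimum of three), the DE is 1.04–1.08 and the error rate about 5.5–5.9%.
- **That omitting the stratum adds to the inflation.** Ignoring a balanced stratification factor generally makes a test conservative.

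**Conclusion.** The point holds in conditional form. The plan randomises and powers by clinic, but its A-versus-B analysis names no clinic effect and no cluster-level unit. If the t-test or rank tests are run on individual patients, the true two-sided error rate for the primary implementation outcome is 9.8% at 21 per clinic and 10.7% at 25. If they are run on the 20 clinic proportions, it is about 4–5%. These figures assume the plan's ICC of 0.02, equal clinic sizes and ten clinics per arm.

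The matter should be settled before analysis, because it governs the primary randomised test.

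A reader might also infer that the trial is underpowered. That goes too far: with an 18-df clinic-level test, power is about 76% at 420 patients but about 80% if all 500 contribute, and 500 is the number the plan enrols.

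**What to change.** Name one primary analysis for the proportion receiving neck-specific exercise, either:

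- a comparison of the 20 clinic proportions between groups, adjusted for the clinic-size stratum (t distribution with 17 df; 18 without the stratum); or
- a logistic mixed model or GEE on patient data with a clinic effect, the stratum as covariate and a small-sample correction for 20 clusters.

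State that patient-level t-tests, Mann-Whitney and Kruskal-Wallis tests will not be used for A versus B, and remove the data-dependent choice for this outcome. Report the difference in proportions with its confidence interval and the estimated ICC. If the linear mixed model is kept for other implementation outcomes, state its random effects, including clinic. Optionally, add that power with the clinic-level test is about 76% at 420 patients and about 80% at 500.

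The cost is wording only: no new data and no more patients. The stated power at 420 becomes about 4 points less favourable (80% to about 76%).
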